## Discussion

The present registry-based controlled cohort study (EASE-IT TF) aims to assess the procedural and clinical outcomes of TF-TAVI with the Edwards SAPIEN 3 PHV when BAV is performed, compared to when the BAV step is omitted. Analysis of the resulting data should provide insight into the clinical relevance and value of BAV in TF-TAVI, and also reveal possible patient variables associated with different outcomes. These findings will have several notable implications for clinical practise.

Despite a number of groups reporting the feasibility and safety of direct TF-TAVI with the Edwards SAPIEN PHV [8, 10, 13, 16], the relative impact of this technique on clinical outcomes has not been properly verified due to methodological limitations of existing comparative studies. As a well-designed, two-arm, fully-prospective, real-world registry, EASE-IT TF will shed light on the potential for direct TF-TAVI to reduce the incidence of the most eminent serious adverse events currently facing TF-TAVI patients. Most notably, these include stroke, AKI, MI, conduction disturbances requiring permanent PPI, and mortality.

Stroke has been previously identified as a predictor of early and medium-term mortality in TAVI patients [17]. It is thought that stroke during TAVI occurs due to dislodgement of embolic fragments from the valve and access vessels caused by the extensive movement of catheters and guide wires, BAV, and PHV expansion. In a study by Reinsfelt et al. using intraoperative transcranial Doppler imaging, 282 cerebral microembolic signals (MES) were recorded in patients undergoing routine TAVI, of which 37 % were generated during instrumentation and 22 % during BAV [18]. A similar Doppler-based study by Erdoes et al. detected a median of 580 intraoperative cerebral high-intensity transient signals (HITS) in TF-TAVI patients, with 28 % generated during instrumentation and 11 % during BAV [7]. A further study by Drews et al. detected medians of 435 and 471 HITS and 78 and 62 MES in the right and left middle cerebral arteries of TAVI patients, respectively, with particular peaks during BAV and PHV positioning [6]. These studies suggest that elimination of BAV from the TAVI procedure (thereby also reducing instrument manipulation) may reduce stroke risk, and potentially minimise other thromboembolic outcomes such as MI. EASE-IT TF will be valuable for testing this hypothesis.

A frequently observed clinical complication of TAVI is AKI, which has been documented in around 16 % of patients and is associated with poor prognosis [19–22]. One factor that may contribute to AKI is the volume of contrast agent used. Van Linden et al. reported a significant correlation between intraoperative contrast agent volume and postoperative AKI in 270 consecutive patients undergoing TA-TAVI with the Edwards SAPIEN PHV [22]. In particular, use of >99 ml of contrast agent was an independent predictor of AKI. Concurrently, a study by Yamamoto et al. in a cohort of 415 elderly TF-TAVI patients found that subjects experiencing post-procedural AKI had been exposed to greater contrast agent doses, and multivariate analysis confirmed the association [21]. Furthermore, a study by Madershahian et al. including 50 patients with pre-existing renal impairment undergoing TA-TAVI with the Edwards SAPIEN PHV found a significantly greater prevalence of acute contrast-induced nephropathy in patients receiving >100 mL contrast agent compared to those receiving <100 mL (69.2 % vs. 41.7 %, respectively) [23]. It therefore appears that reducing contrast agent volume may reduce AKI rates. Importantly, several studies report that direct TAVI significantly reduces contrast agent volumes [8, 13], indicating the potential for this to translate into reduced AKI. Again, results from the EASE-IT TF registry will help to clarify this idea.

Conduction disturbances requiring PPI have been reported to occur in 13–25 % of patients undergoing TAVI [3, 24]. In PARTNER, patients requiring PPI had longer postoperative hospitalisation times (7.3 days vs. 6.2 days), higher frequencies of repeat hospitalisations up to 1 year (23.9 % vs. 18.2 %) and increased mortality or repeat hospitalisation up to 1 year (42.0 % vs. 32.6 %) [25]. Therefore, reducing PPI requirement is clearly desirable. In a study by Gensas et al., BAV was identified as an independent predictor of PPI requirement [3]. Concurrently, findings by Grube et al., Fiorina et al. and Islas et al. suggest that PPI rate is lower in patients undergoing direct TF-TAVI compared to standard TF-TAVI (11.7 % vs. 27.8 %, 5.5 % vs. 15.5 %, and 6.3 % vs. 14.1 %, respectively). Conversely, Conradi et al. found no significant difference in PPI rate between the two procedural variants (both 15.4 %). Therefore, the effect of BAV on PPI requirement requires additional investigation, which the EASE-IT TF study will provide.

In addition to identifying potential benefits, the EASE-IT TF study may also reveal negative outcomes associated with direct TF-TAVI. These may include the need for post-procedural BAV, which has already been noted in 16.7–34 % of patients undergoing direct TF-TAVI with the CoreValve PHV [1, 11, 12] and 0–13.7 % of patients with an Edwards SAPIEN PHV [8, 13, 16]. Data gathered in EASE-IT TF will provide additional comparative evidence on this, and other complications of direct TF-TAVI.

Taking everything into account, EASE-IT TF should provide invaluable information from which to make well-informed recommendations about the costs/benefits of performing BAV in TF-TAVI. The planned analysis to identify specific patient characteristics associated with more or less favourable outcomes (for example, exclusion of BAV is associated with reduced AKI rate in patients with existing kidney disease, while detrimental in patients with reduced left ventricular ejection fraction) has the potential to offer valuable insight into the appropriateness of BAV in distinct patient subsets. In terms of future developments within the field, EASE-IT TF will promote critical consideration of the currently adopted TAVI method, and may lead to refinement of technical guidelines.

### Potential limitations of EAE-IT TF

As an observational study, EASE-IT TF is extremely useful for providing real-world information that is directly applicable to clinical practise, but has several potential limitations. Firstly, physicians are free to place patients in either direct TF-TAVI or standard TF-TAVI groups at their discretion, which may mean more patients with a certain characteristic (i.e., higher Euro-SCORE) are concentrated in a particular group. This lack of randomisation may produce distinct study arm populations, limiting validity of subsequent inter-group comparisons. However, this is unavoidable if we wish to assess the benefits of direct TF-TAVI in patients that physicians consider eligible in the real world. By asking investigators to justify their decision, we gain valuable information about the criteria currently deemed indicative for TF-TAVI with or without BAV. This will enable us to reflect upon the reliability of these factors for determining direct TF-TAVI eligibility, and provide further recommendations. Secondly, the fact that a 1:1 group assignment ratio is not obligatory may result in smaller patient numbers in one study arm, potentially reducing statistical power. Again, this is an inherent and unavoidable problem when examining real-world circumstances. Thirdly, compared to most clinical trials, observational registry data tends to contain more omissions and inaccuracies. However, monitoring following database closure is planned, and will ensure verification of source data in a reasonable sample of enrolled patients to minimise this limitation. Finally, only a 6-month follow-up is planned, which may be inadequate to detect the effect of direct TF-TAVI on long-term outcomes. Further studies may therefore be required to evaluate these long-term consequences. Though essential for validity, the use of a single PHV type (Edward SAPIEN 3) in EASE-IT TF means that findings will be limited to TF-TAVI with this specific device. Therefore, further studies assessing the clinical value of BAV using other PHVs will be necessary. The same is true for alternative delivery systems, access routes and patient groups.

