Several pilot studies in high surgical risk patients undergoing TF-TAVI without prior BAV (direct TF-TAVI) have been published to date. An early pilot study by Grube et al. in 60 consecutive patients undergoing direct TF-TAVI with the Medtronic CoreValve PHV described a 96.7 % procedural success rate, with in-hospital mortality, stroke, major vascular complication, and myocardial infarction (MI) rates of 6.7, 5, 10, and 0 %, respectively [1]. Concurrently, a similar pilot study by Mendiz et al. using the same PHV demonstrated that direct TF-TAVI in 51 patients led to a procedural success rate of 94.2 %, with PPI, stroke and all-cause mortality rates of in 27.5, 3.9, and 3.9 % at 30 days [11]. Most recently, a larger retrospective study enrolling 163 patients found that direct TF-TAVI with the SAPIEN 3 PHV was feasible in 94.5 % of cases, and had an all-cause mortality rate of 3.7 % at 30 days [10]. BAV was required to overcome crossing difficulties in only 5.5 % of patients, who were generally older, had a higher calcium score, higher transvalvular gradients, and smaller AVA. Thus, pilot studies have demonstrated the feasibility of direct TF-TAVI in the majority of standard TF-TAVI candidates; though suggest that further studies to identify characteristics of patients for whom the technique is most appropriate would be useful.

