### Patient selection

In order to be included in the study, patients are required to meet all of the following criteria: 1) indication for TF-TAVI according to the IFU for the Edwards SAPIEN 3 PHV, 2) age ≥18 years, 3) signed ICF. All patients meeting any of the following criteria will be excluded from the study: 1) contraindications for TAVI via the TF access route according to the Edwards SAPIEN 3 IFU, 2) logistic Euro-SCORE I >40 %, 3) mitral or tricuspid valvular insufficiency > grade II, 4) uncontrolled atrial fibrillation (no rhythm control established), 5) left ventricular or atrial thrombus identified via echocardiography, 6) previous aortic valve replacement, 7) mobile structures on leaflets, 8) requirement for a cerebral protection device, and 9) high probability of non-adherence to follow-up requirements based on social, psychological or medical grounds. So as to avoid influencing investigator decision to perform TF-TAVI with or without BAV, enrolment in the register will occur after this choice had already been made, and a 1:1 ratio will not be strictly pursued (Fig. 1). Reasons for this decision and any subsequent changes will be systematically documented. Subjects withdrawing consent will be omitted from the registry and not replaced.

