### TF-TAVI procedure

Investigators are free to perform TF-TAVI using the Edwards SAPIEN 3 PHV according to locally-adopted techniques. Patients in the standard TF-TAVI group will undergo the procedure with pre-deployment BAV, while those in the direct TF-TAVI group will undergo the procedure without pre-deployment BAV.

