### Data collection

Data on enrolled patients will be collected via electronic case report forms (eCRFs) using registry identification numbers rather than names, to protect identity. eCRFs will be completed for the visit prior to implantation, on the day of implantation, and at follow-up visits 30 ± 7 days and 6 months (±14 days) post-implantation, and signed at the earliest opportunity by either the investigator or designated responsible party (Table 1). The results of pre-TAVI echo and CT assessment will be documented as well as potential reasons for or against opting for BAV in a given patient. Additionally, reports of device-related serious adverse events or death must be provided within 48 h of occurrence. Up to 2 sites (20 %) will be randomly selected for monitoring purposes following completion of data collection, and subjected to source data verification (expected to be 100 % for stroke, life-threatening or major bleeding, renal failure, vascular and valve complications, PPI and mortality).

**Table 1 Tab1:** Assessments

Parameter	Admission	Intervention	Discharge	30d FU	6 Mo FU
Inclusion/Exclusion criteria	X				
Demographics	X				
Diagnosis of valve disease	X				
Echocardiography	X				
Computed Tomography	X				
Symptoms	X			X	X
Cardiac baseline characteristics	X				
ECG	X		X		
Comorbidities	X				
Risk scores	X				
Prior cardiovascular intervention	X				
Current medications	X		X	X	X
Interventional details		X			
Interventional results		X			
AE		X	X	X	X
Hospitalization duration			X		
Creatinine value	X		X		X
Early safety/Clinical efficacy				X	X

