### Statistics

To achieve a statistical power of 80 %, the estimated sample size needed to detect an absolute risk reduction of 13 % at 30 days post-TAVI was 180 evaluable patients. This calculation was based on the 30-day event rates reported by a previous study on direct TF-TAVI by Grube et al. [1]. In order to accommodate an approximate drop out rate of 10 % (20 patients) during the first 30 days, a final necessary sample size of 200 patients was established.

Analysis for all patients in the registry will be performed from an intention-to-treat perspective. The collected data will be presented and summarised using descriptive statistics. Categorical variables will be reported as frequency distributions, while continuous variables will be reported as mean (± standard deviation) and median (range) values. Where appropriate, actuarial probability and linearised rates may be used to report on adverse events. Survival (and adverse event outcomes, where appropriate) will be analysed using the Kaplan-Meier method.

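### The first aim and the sample size rest on comparing arms that physicians choose, but no stated analysis controls confounding and the loss of validity is accepted as unavoidable

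*Protocol article*

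**What the plan says.** **How the arms arise.** The limitations section of the Protocol article states that "physicians are free to place patients in either direct TF-TAVI or standard TF-TAVI groups at their discretion". Patient selection adds that "enrolment in the register will occur after this choice had already been made, and a 1:1 ratio will not be strictly pursued".

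**What the comparison is for.** The Abstract puts determining the risks and benefits of direct versus standard TF-TAVI first, and associations between patient variables and outcomes second. The Statistics section sizes the study on a 13-point absolute risk reduction at 30 days with 80 % power: 180 evaluable patients, 200 enrolled.

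**What analysis is stated.** From the Statistics section: "The collected data will be presented and summarised using descriptive statistics". Actuarial probabilities and linearised rates may be used for adverse events, and survival is analysed by Kaplan-Meier. The section takes an intention-to-treat perspective. No regression adjustment, matching, weighting, stratification or sensitivity analysis for confounding is named anywhere in the article.

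**What is said about imbalance.** The limitations section expects that "more patients with a certain characteristic (i.e., higher Euro-SCORE) are concentrated in a particular group" and continues: "This lack of randomisation may produce distinct study arm populations, limiting validity of subsequent inter-group comparisons. However, this is unavoidable". That sentence goes on to make the point conditional on wanting to study patients whom physicians judge eligible in practice. The recorded reasons for each decision are to be used to reflect on eligibility criteria.

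**What is collected.** Data collection: "The results of pre-TAVI echo and CT assessment will be documented as well as potential reasons for or against opting for BAV". Table 1 lists demographics, echocardiography, CT, ECG, comorbidities, risk scores and creatinine at admission.

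**The concern.** Two statements are run together. One is that the arms will differ because nobody randomises; in a registry that is true. The other is that the comparison must therefore be read with its bias left in; that does not follow. Baseline variables that plausibly drive both the BAV decision and the 30-day composite are on the case report form, and the article gives them no role in the between-arm contrast.

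If the analysis is run as written, a difference in the composite mixes any effect of BAV with differences in who was selected for it. The bias can go either way. If more difficult valves are steered towards BAV, direct TF-TAVI looks better than it is; if sicker patients are spared BAV, it looks worse. The Discussion nevertheless expects recommendations on performing BAV and possible refinement of technical guidelines. The Background also faults an earlier 249-patient comparison for forming groups in a way that may have biased its populations, which is the same weakness.

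**Working it through.** **1. The plan's own figure.** 180 / (1 − 0.10) = 200, so the dropout inflation reproduces. The 180 can be neither confirmed nor refuted, because alpha, sidedness and the two event rates are not stated. This point does not depend on it; what matters is that the sample size is set on a between-arm difference.

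**2. The passages side by side.**
- Aim (Abstract) and sample size (Statistics): a comparison of direct with standard TF-TAVI.
- Assignment (Patient selection; limitations): by physician choice, before enrolment.
- Methods (Statistics): descriptive, actuarial or linearised, Kaplan-Meier. Each summarises an arm as observed; none makes the arms comparable.
- Response to the conceded problem (limitations): record the reasons and reflect on eligibility. That informs future selection and does not correct the contrast.
- The second aim (Abstract, Background, Discussion) looks for patient characteristics linked to outcome. It has no stated method, and the Discussion presents it as finding subsets who do better or worse, which is not control of confounding.

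**3. What a crude contrast could show with no BAV effect (illustration only).** The inputs below are assumptions; none comes from the article. Take one binary risk factor with prevalence q_S in the standard arm and q_D in the direct arm, baseline risk b, risk ratio RR, and 90 patients per arm (180 / 2; the article does not promise equal arms).

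Arm risk: p = b(1 − q) + b·RR·q. Hence the spurious difference is b(RR − 1)(q_S − q_D).

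Example: b = 0.15, RR = 2, q_S = 0.70, q_D = 0.30.
- p_S = 0.15 × 0.30 + 0.30 × 0.70 = 0.255
- p_D = 0.15 × 0.70 + 0.30 × 0.30 = 0.195
- difference = 0.15 × 1 × 0.40 = 0.060

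Chance that a two-sided 5 % test is significant in that direction, by the normal approximation with p̄ = (p_S + p_D)/2 and n = 90: Φ{[p_S − p_D − 1.96·√(2p̄(1 − p̄)/n)] / √([p_S(1 − p_S) + p_D(1 − p_D)]/n)} = Φ{(0.060 − 0.122)/0.0621} = 0.159. With no confounding it would be 0.025.

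| b | RR | q_S / q_D | p_S vs p_D | Spurious points | Chance of significance in that direction |
|---|---|---|---|---|---|
| 0.15 | 1.5 | 0.6 / 0.4 | 19.5 % vs 18.0 % | 1.5 | 4.4 % |
| 0.20 | 2.0 | 0.6 / 0.4 | 32.0 % vs 28.0 % | 4.0 | 8.4 % |
| 0.15 | 2.0 | 0.7 / 0.3 | 25.5 % vs 19.5 % | 6.0 | 15.9 % |
| 0.20 | 2.5 | 0.7 / 0.3 | 41.0 % vs 29.0 % | 12.0 | 39.2 % |

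The range is 1.5 to 12 points against a design difference of 13. The table shows that the mechanism can matter at the scale the study is built to detect. It does not estimate the bias in this registry.

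**The case against.** The strongest objection is that this is a condensed article. Adjustment methods commonly sit in a full protocol or analysis plan, and the Statistics section names no between-arm test or estimator at all, so it never says that the comparison will be crude. That stands in part: a reader might infer that the final analysis will be unadjusted, and the document does not establish this. The point survives because the article does more than stay silent. It raises the bias, concedes that it limits validity, and offers acceptance as the answer.

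The authors also disclose the limitation openly, and their remark about what is unavoidable refers to the lack of randomisation and the differing populations. Both are fair. The fault is that no mitigation is stated beside a comparative first aim, and nothing is concealed.

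Three stronger readings are tempting and not supported:

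- *That the article itself lists the confounders.* Only EuroSCORE is named as a possible imbalance. The Background's description of patients "who were generally older, had a higher calcium score, higher transvalvular gradients, and smaller AVA" concerns those who needed BAV for crossing difficulty in another study's 163-patient direct TF-TAVI cohort (5.5 %, about 9 patients). These are sensible candidates for adjustment, but that is the reviewer's inference.
- *That confidence intervals are too narrow because technique clusters by site.* The TF-TAVI procedure section says "Investigators are free to perform TF-TAVI using the Edwards SAPIEN 3 PHV according to locally-adopted techniques", which might suggest site-level choice. Data collection and the limitations section describe a decision made for each patient, and no intracluster correlation is given. No inflation of type I error can be claimed on this ground.
- *That the illustrative figures measure this study.* They do not; every input is assumed.

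**Conclusion.** The point holds for the analysis as the article states it. The first aim and the sample size depend on a between-arm contrast, physicians form the arms, none of the named methods controls confounding, and the resulting loss of validity is accepted although baseline data that would allow adjustment are collected. Followed as written, a crude 30-day difference could not be attributed to omitting BAV.

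The size of the bias is unknown. The illustration gives 1.5 to 12 spurious points under assumed inputs and serves only to show that the problem need not be small relative to 13 points. The conclusion rests on the text and not on those figures. It also rests on no unseen plan already providing adjustment; if one does, the remaining correction is to say so in the article.

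**What to change.** In the Statistics section, and in the analysis plan if it is not already there, make the primary 30-day between-arm comparison an adjusted one:

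- Define the arms by the decision made before enrolment, in line with the stated intention-to-treat perspective.
- Prespecify a short set of baseline prognostic covariates, for example age, EuroSCORE, valve calcification, gradient or AVA, baseline creatinine, and baseline conduction status where recorded. With about 180 evaluable patients the smaller arm has at most 90, so a long list is not affordable. Table 1 gives only headings, so confirm that each item is captured in usable form.
- Fit a propensity score and use overlap weighting or a similar method.
- Report the adjusted risk difference with a 95 % CI and standardised differences before and after adjustment. Keep crude rates as a supplementary table.
- Account for site if both techniques are used within sites. Where a site uses only one technique, its effect cannot be separated from that of BAV, and the report should say so.
- Use the recorded decision reasons to guide covariate choice and to check overlap. Do not enter them automatically in the propensity model: a reason that almost fixes the arm destroys overlap.

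In the limitations section, separate the lack of randomisation, which is unavoidable, from the handling of imbalance, which is a choice, and say that unmeasured confounding remains.

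The cost is wording, modest extra analysis and somewhat wider intervals. No new data should be needed if the listed items are recorded as Table 1 suggests.
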